### Procedures

Before data collection, the research team will train four Swahili speaking research assistants in data collection. They will be blind regarding the allocation of the schools. A standardized introduction and questionnaire administration procedures will be developed to ensure high objectivity and reliability during data assessment. All questionnaires will be administered in Swahili. Following established international guidelines [52], Swahili native speakers will translate all measures that are not available in Swahili from English to Swahili and then back to English in a blind written form. The back-translated measures will then be compared with the original measures to ensure correct translation and equivalence of the content. A pilot study at one primary school (not included in the trial) will be conducted to ensure the feasibility of the questionnaire administration.

Prior to data collection, a letter explaining the study aims and procedures will be sent together with an informed consent form to the parents to seek parental consent. To ensure common and clear understanding of the relevant details of the study, the research team will provide information to all selected students in a formal information session. Students who provide assent and whose parents have signed the informed consent form will be invited to fill out questionnaires in groups of two to four students on the school grounds under supervision of a research assistant. To ensure sufficient privacy, the students will be seated so that it will be impossible for anyone to see how the questions are being answered. The completion of questionnaires will take an average of 45 min at baseline and follow-up.

After being introduced to the project’s objectives, the teachers will be invited to participate in the study. Teachers willing to participate will be requested to sign an informed consent form and to fill out a questionnaire in their free time between lessons under the guidance of an assessor in a one-to-one setting. The completion of the questionnaires will take, on average, 30 min at baseline and at follow-up assessment.

### Intervention

In the intervention schools, the *ICC-T *intervention will be implemented for 5.5 days (8 h on a full day).* ICC-T* is based on attachment, behavioral, and social learning theories. *ICC-T* includes sessions on (a) teacher–child communication and interaction, (b) violence prevention, (c) effective non-violent discipline strategies, and (d) identifying and supporting burdened children (for more details see [1, 2, 6]). *ICC-T* intervention in the selected schools will be implemented by one main facilitator with the assistance of two assistant facilitators. All facilitators are trained Tanzanian psychologists and teachers. *ICC-T* materials for training as well as presentations and discussion during trainings will be in Swahili. Participation of the training will be free of charge. Food and beverage will be provided to participants as well as transport compensation of US$4 per day. Prior to the official participation in the training, teachers will be offered introductory letters informing them of the voluntary nature of their participation as well as their right to withdraw from the training at any point. Teachers who have agreed to participate will sign the training informed consent form. Confidentiality of information shared during the training will be ensured. No personal information will be shared with external sources.

### Control

At the monitoring schools no intervention will be implemented. The research team will also have close contact with the monitoring schools to ensure that teachers do not receive any training of the same nature during the study duration. Data assessment at monitoring schools will be conducted both at pre-assessment and follow-up phases.

### Outcome measures

Our study intends to test the effects of *ICC-T* on the use of violent discipline by teachers at school. This primary outcome measure will be assessed by students’ self-reported experiences of violence as well as teachers’ self-reported use of violence. Secondary outcome measures include teachers’ attitudes towards violent discipline, children’s mental health and well-being, as well as students’ school performance (provided by the school administration). Purpose-built measures adapted from previous studies [1, 6] will be used to assess the feasibility of ICC-T at the primary school level. We follow the guidelines for feasibility studies in assessing the demand, applicability, acceptability, and integration of *ICC-T* core elements in the teachers’ daily work [53].

#### Children

##### Experience of violence

At pre-assessment and at follow-up assessment, we will use the Conflict Tactic Scale (CTS) [54] to capture student’s experiences of violence by teachers. Students’ exposure to violence by teachers will be assessed using the physical violence and the emotional violence subscales of the CTS. Thirteen items assessing physical violence and five items measuring emotional violence subscales will be applied. The scale items are answered on a seven-point Likert scale ranging from 0 (this has never happened) to 6 (more than 20 times) and the sum score ranges from 0 to 78 for physical violence and from 0 to 30 for emotional violence. Subscale scores are derived by summing up all item scores. The CTS presented with acceptable internal consistency of 0.88 in a Ugandan student sample [22]. The CTS scale has been used in East African student samples and has demonstrated its utility in assessing students’ exposure to violence by teachers [1, 5, 22].

##### Mental health problems

We will use the Strength and Difficulties Questionnaire (SDQ) to assess children’s mental health problems at pre-assessment and at follow-up assessment. The items are assessed using a three-point Likert scale ranging from 0 (not true) to 2 (certainly true). Reversed items are recorded before the computation of the total scale score (sum of scores for all items excluding the five items of the prosocial behavior subscale) that ranges between 0 and 40, with a score above 20 representing the presence of mental health problems. The Cronbach alpha reliability of the total difficult score was 0.82 in the validation study [55]. The SDQ scale has been tested in the Tanzanian population and proved its usefulness in screening for mental health problems [34, 39, 40, 56].

##### Academic performance

In addition, we will assess students’ academic performance. The students’ scores in mathematics, Swahili, English, science, social science, and general studies in the mid-term exam will be provided by the school administration.

#### Teachers

##### Use of violent discipline

We will use a modified version of the CTS which was initially developed to assess parents’ reports on their use of violence to assess teachers’ use of physical and emotional violence in schools (see above for more details on subscales and answer categories). The scale has been implemented in similar studies in East Africa [1, 2]. The CTS presented with acceptable internal consistency of 0.76 in a Ugandan teacher sample [22]. The CTS scale has proved its usefulness in assessing teachers’ self-reported use of violence in the classroom [5, 22].

##### Attitude towards discipline

We will use an adaptation of the CTS to assess teacher’s positive attitude towards the use of violent discipline [1]. The items are the same as described before but this time answered on a four-point Likert scale ranging from 0 (never OK) to 3 (always or almost always OK). The scores for each subscale are then summed up to one score for physical assault and one for emotional violence. In a study with Ugandan teachers the Cronbach alpha coefficient was 0.80 for the total score [22]. The modified CTS scale has been used in East African teacher samples and it proved its usefulness in assessing teachers’ self-reported attitudes towards violence in the classroom [1, 22].

##### Purpose-built measures for ICC-T training evaluation

We will adopt the purpose-built measures as used in previous studies conducted by our team [1, 2, 6]. We will follow the guidelines for feasibility studies by Bowen et al. [53] in assessing the demand, applicability, acceptability, and integration of *ICC-T* training techniques into teachers’ daily work. We will assess participant’s expectations regarding the workshop and its relevance in their daily work before the intervention, directly after the intervention, and at the follow-up stage. Additionally, acceptability of the training (i.e., satisfaction with the training and evaluation of new knowledge acquired) will be assessed after the intervention and at the follow-up stage. Lastly, teachers’ incorporation of the *ICC-T *core elements into their daily school work will be assessed after the intervention and at the follow-up stage.

### Measures against bias

The stratified random sampling approach will minimize recruitment bias. Our careful selection of the assessment instruments will minimize bias based on the use of unvalidated outcome measures. As the allocation will be executed at the cluster level and by the core research team, those conducting data collection will be blind to the treatment conditions of the schools. Though the intervention participants will not be blind in regard to whether they belong to the intervention or the monitoring group, violence by teachers will also be assessed by assessing students’ self-reported exposure to violence. Analysis will be carried out based on the groups as randomized (‘intention to treat’) to avoid incomplete accounting of participants and outcome events. The trial has been registered in a trial registry for clinical studies and a study protocol paper will be published to avoid selective outcome reporting.

### Ethics procedures

Considering that this study involves human subjects, specifically children who are considered a vulnerable group, it is important to obtain ethics clearance from the relevant ethics boards. This study has obtained ethics clearance from the Ethics Review Boards of Bielefeld University (number 2018–234) and the University of Dar es Salaam (number AB3/12(B)), Tanzania. During data assessment, only pre-assigned codes will appear on the questionnaires. Data will be stored on a password-secured computer accessible only to the study investigators. Personal data obtained during the research will be kept confidential and will not be disclosed to any other person without the participant’s permission or as required by the law. Behavioral intervention studies are minimum risk studies. In the event that there are any unexpected adverse effects, however, the researchers will document and report such occurrences to the trained psychologist on the research team. In case the problem is severe, the researcher will report the problem to the respective ethics bodies within one week. Questions about experiences may evoke upsetting memories in the event that the participant experienced similar events in his or her life. Participants who will experience any severe psychological distress during the course of the data collection will be provided with psychological support by a research team member. For participants who experience adverse or unexpected events, appropriate referrals and follow-up for specialized services and further management will be made on a case-by-case basis.

### Data analysis

Pre-assessment data will be used to provide information about the prevalence of maltreatment and violence in different settings as well as children’s mental health and well-being. Longitudinal analysis will be carried out based on the groups as randomized (intention to treat). We will use the last-observation-carried-forward approach; i.e., in drop-outs we assume no change from pre-assessment to follow-up. Results will be presented including appropriate effects sizes and with a measure of precision (95% confidence intervals). Our main analysis of the primary and secondary outcomes will be time × group interaction effects using repeated multivariate analysis of variance (MANOVA). In case of a noted cluster effect (intra-cluster correlation coefficient > 0.10) we will use multilevel analysis. Multivariate interaction effects and univariate interaction effects of each outcome variable will be tested first. Paired *t*-test analysis will examine the differences from the pre- to follow-up assessment in the intervention group while independent *t*-test will examine whether there is a difference between the control group and intervention group at the follow-up assessment. Effect size η^2^ ≥ 0.01, η^2^ ≥ 0.06 and η^2^ ≥ 0.14 will be considered to represent a small, moderate, and large effect, respectively [57]. For *t*-tests, effect size interpretation will be guided by the suggestion of Cohen where d ≥ 0.20, d ≥ 0.50, and d ≥ 0.80 will represent a small, medium, and large effect, respectively [57].

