## Methods/design

### Design of the study

Using a two-arm matched cluster randomized controlled trial, the study will include 12 schools from six regions in Tanzania. From each region one school will be randomly allocated to the intervention school condition (from which all teachers will be trained in an ICC-T intervention workshop) and the other to the monitoring school condition (which receive no intervention). The study will have two data collection phases: pre-assessment directly before the intervention (t0) and follow-up assessment approximately 6 months after intervention (t1). See Figs. 1 and 2 and the SPIRIT 2013 Checklist: Recommended items to address in a clinical trial protocol and related documents (Additional file 1).

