Within each of the selected schools, 40 pupils from of the fifth and 40 pupils from sixth year of formal schooling will be stratified by gender and then randomly selected. Thus, the target sample will be 960 pupils. Based on a study that used a similar design [1], we would expect moderate to large effects on pupils’ self-reported exposure to violence. An a priori power analysis (α = 0.05, power = 0.80, moderate effect size of ƒ = 0.25) indicated a required total sample size of at least *n* = 128 pupils to detect significant interaction effects. To adjust for the nested design of the study, we calculated the following design effect (DE): DE = 1 + (fixed cluster size considering drop-outs − 1) × intra-cluster correlation coefficient. Considering 80 pupils per school, a dropout rate of 20%, and an intra-cluster correlation coefficient of 0.05, the DE for the pupil sample is 4.15, which results in a required sample size of at least 532 pupils. All teachers at the selected schools will be included in the study sample. Our target sample will be at least 20 teachers per school, resulting in a total sample of at least 240 teachers. Based on the previous study, we would also expect moderate to large effects on teachers’ self-reported use of violence against students. The a priori power analysis (see above for details) indicated a required total sample size of at least *n* = 128 teachers to detect significant interaction effects. To adjust for the nested design of the study, we again calculated the DE. Considering a minimum of 20 teachers per school, a drop-out rate of 20% and intra-cluster correlation coefficient of 0.05, the DE for the teacher sample is 1.8, which results in a required sample size of at least 231 teachers.

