Due to the longitudinal and experimental nature of this study, we are prepared to face a number of challenges which may result in limitations of the study. The potential challenges include some eligible participants refusing to participate in the study, as well as potential drop-outs at any stage of the project. Attrition among participating students and teachers may occur for a number of reasons, including possible transfers from one school to another as well as truancy and absenteeism. In respect to individual’s right to participation, the study team will ensure that participation in the study is entirely voluntary and any participant seeking to drop out from the study at any stage is free to do so. Though we will do our best to keep the attrition rate as low as possible, this may affect the potential findings. In addition, self-reported questionnaires are susceptible to possible bias of respondents and to social desirability. Furthermore, there are strong socio-cultural factors, attitudes, and beliefs that support the use of violence against children. The expected changes in attitudes and behavior can be considered only preliminary. In addition, the inclusion of relatively few schools limits the generalizability of the study results.

Despite these potential limitations, we believe that the study will contribute important new findings regarding the feasibility and effectiveness of *ICC-T* as one school-based preventative intervention approach to reduce violence by teachers. Furthermore, we presume that our study will contribute significantly to the global campaign to end violence against children [3, 4, 49] and therefore support the efforts made by the government of Tanzania to reduce violence against children in all settings. We therefore anticipate that, with successful evaluation of the *ICC-T* at the primary school level, the government, non-governmental organizations, policy makers, and other education stakeholders in Tanzania and other Sub-Saharan Africa countries will recognize the potential of school-based interventions in general and *ICC-T* in particular. It is hoped that this will lead relevant stakeholders to consider possibilities to scale up the intervention at the regional or national levels, integrating it in the regular teacher training programs.

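### With only two assessments, carrying the last observation forward enters a zero change for every drop-out, which shrinks the estimated effect and misplaces its confidence interval

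*Protocol article*

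**What the plan says.** The Data analysis section of the protocol article gives one rule for missing follow-up: "We will use the last-observation-carried-forward approach; i.e., in drop-outs we assume no change from pre-assessment to follow-up". It appears next to the commitment to analyse by randomised group, and no other handling or sensitivity analysis is named.

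The rule acts on these parts of the plan:

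- Design of the study sets two assessments: "pre-assessment directly before the intervention (t0) and follow-up assessment approximately 6 months after intervention (t1").
- The main test is set in Data analysis: "Our main analysis of the primary and secondary outcomes will be time × group interaction effects using repeated multivariate analysis of variance (MANOVA").
- The same section adds a between-arm test at follow-up: "independent *t*-test will examine whether there is a difference between the control group and intervention group at the follow-up assessment".
- It also promises intervals: "Results will be presented including appropriate effects sizes and with a measure of precision (95% confidence intervals").
- The sample-size text under Participants allows for "a dropout rate of 20%, and an intra-cluster correlation coefficient of 0.05" among pupils, and uses the same two values for teachers.
- The Discussion attributes expected attrition to "possible transfers from one school to another as well as truancy and absenteeism".

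**The concern.** In a trial with many visits, the last observation may be a late one. Here the only earlier observation is the score from before the intervention, so the rule is baseline carried forward. The interaction is the difference between arms in mean change, and the rule inserts a fixed zero into that quantity for every drop-out and treats it as observed.

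Nothing in the article argues that a pupil who transfers or is absent, or a teacher who moves, would have shown no change. The study hypothesis is that the intervention does produce change. Intention to treat fixes which arm a participant counts in; it does not say what value a missing score should take.

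The size of the effect and its confidence interval are at stake for every primary and secondary outcome measured at both assessments.

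**Working it through.** **The plan's own figures.** The article plans on f = 0.25, that is d = 2 × 0.25 = 0.50, with α = 0.05 and power 0.80. A two-sided t-test with 64 per arm (128 in total) has power 0.801, so the 128 reproduces. For pupils, 80 × 0.8 = 64 remain per school; DE = 1 + (64 − 1) × 0.05 = 4.15, and 128 × 4.15 = 531.2, rounded up to 532. For teachers, 20 × 0.8 = 16; DE = 1 + (16 − 1) × 0.05 = 1.75, given as 1.8, and 128 × 1.8 = 230.4, rounded up to 231.

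**Inputs.** From the article: 6 schools per arm, 80 pupils or at least 20 teachers per school, drop-out 20%, intra-cluster correlation 0.05, effect 0.50. Assumed, because the article does not give them: SD of the change score = 1, true effect δ = −0.50 (a reduction), the intra-cluster correlation applying to the change score, drop-out unrelated to outcome, and the values of control-arm change c and arm-specific drop-out (dI, dC) used below.

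**Expected estimate.** Under the rule the interaction estimates

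(1 − dI)(c + δ) − (1 − dC)c = (1 − dI)δ + (dC − dI)c.

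- Equal drop-out of 10%, 20% or 30%: −0.45, −0.40 or −0.35, whatever the value of c.
- At 20%, re-standardised by the SD of the carried-forward changes with c = 0: 0.40 / √((0.84 + 0.80)/2) = 0.44. A true effect at the article's threshold for medium (0.50) would fall below it.
- No true effect, c = −0.3, drop-out 10% intervention and 30% control: 0.20 × (−0.3) = −0.06, a spurious benefit. With the drop-out rates reversed it is +0.06.
- c = 0: the second term vanishes, so unequal attrition can only attenuate.

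**Standard error.** Per arm, the variance of a carried-forward change is (1 − d)σ² + d(1 − d)μ², where μ is that arm's mean change. With d = 0.2, δ = −0.50 and c = 0 this is 0.84 (intervention) and 0.80 (control). The observed-data equivalent is 1/0.8 = 1.25 in each arm. The SE ratio is √(1.64/2.50) = 0.81. It stays at 0.80 to 0.85 for c between −0.5 and +0.5, and rises to 0.92 at c = −1.

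**Simulation.** To isolate the missing-data rule from the separate question of clustering, inference used unpaired school means with t intervals on 10 degrees of freedom. Drop-out was 20% in both arms, δ = −0.50, c = 0:

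| | Pupils, carried forward | Pupils, observed | Teachers, carried forward | Teachers, observed |
|---|---|---|---|---|
| Mean estimate | −0.40 | −0.50 | −0.40 | −0.50 |
| Sampling SD | 0.118 | 0.147 | 0.154 | 0.191 |
| Reported SE | 0.118 | 0.147 | 0.154 | 0.191 |
| 95% coverage of δ | 88% | 95% | 91% | 95% |
| Power | 86% | 86% | 65% | 66% |

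With δ = 0 and equal drop-out, the rejection rate was about 5% under both methods. With δ = 0, c = −0.3 and 10% v 30% drop-out, the carried-forward test rejected about 7 to 8% of the time for pupils and 6.5% for teachers.

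**The case against.** Several points on the other side stand.

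- A reader might infer that the rule understates the standard error of its own estimate. It does not: reported SE and sampling SD agree. Coverage falls because the interval is centred on a shrunken effect. The SE is small only relative to what the observed data support, and with a very large mean change it can be larger (ratio 1.14 at c = −2).
- A reader might also infer inflated false positives. With equal attrition unrelated to outcome, estimate and SE shrink together, so type I error and power are almost unchanged. The result is then an understated benefit, not a false one.
- Bias away from the null needs unequal attrition together with control-arm change, or outcome-related drop-out. The article gives no arm-specific attrition and no drift, so the 10% v 30% and 0.3 SD values are illustrations. The 0.06 SD they produce is about half a school-level SE.
- The 20% is a sample-size allowance, not a forecast. At 10% the estimate is 0.45 and coverage is 93 to 94% for pupils and 94 to 95% for teachers.
- Missing at random may also fail. A pupil who transfers out of an intervention school is no longer taught by its trained teachers, and under Intervention teachers may decline or leave the training.

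The last point does not rescue the rule. It is a reason to examine departures from missing at random openly, instead of fixing zero change as the only analysis.

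**Conclusion.** The concern holds in a conditional form and should be fixed. The rule is stated in the article, so it is not a detail left to an unseen analysis plan. Given equal attrition and drop-outs who would have changed like those who stayed, 20% loss turns 0.50 SD into 0.40 SD, and the nominal 95% interval covers the true effect about 88% (pupils) or 91% (teachers) of the time. The interval is also narrower than the observed data justify, with an SE about 0.8 of the observed-data value.

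The documents do not support saying that the trial will report a false benefit, or that the hypothesis test is invalid. Those outcomes depend on attrition patterns and drift that the article neither gives nor excludes. Equally, calling the rule conservative relies on conditions that the article does not state and cannot guarantee.

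**What to change.** In Data analysis, replace the carried-forward rule for the primary analysis with a likelihood-based mixed model on all observed pre and post scores. It should include a school effect and a small-sample degrees-of-freedom correction, because there are only 12 schools. Everyone with a baseline score stays in the analysis, so the comparison remains by randomised group. Report attrition by arm for pupils and for teachers. Keep the assumption of no change in drop-outs as one sensitivity analysis, alongside a delta-adjusted one that varies the assumed change in drop-outs by arm.

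The cost is a change of wording and modest programming. No new data are needed, and the article already provides for multilevel analysis if the intra-cluster correlation exceeds 0.10. The drawbacks are reliance on missing at random, which the sensitivity analyses address, and a wider interval that reflects the information actually collected.

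### The analysis allows for school only if the ICC exceeds 0.10, yet the trial is sized on an ICC of 0.05, so the expected analysis ignores the unit of randomisation

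*Protocol article*

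**What the plan says.** The Design of the study section sets the unit of randomisation: "Using a two-arm matched cluster randomized controlled trial, the study will include 12 schools from six regions in Tanzania". One school in each region goes to each arm.

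The Participants section takes 128 pupils as the unadjusted requirement for the interaction effects and then allows for clustering with "DE = 1 + (fixed cluster size considering drop-outs − 1) × intra-cluster correlation coefficient". Its inputs and result are: "Considering 80 pupils per school, a dropout rate of 20%, and an intra-cluster correlation coefficient of 0.05", and "the DE for the pupil sample is 4.15, which results in a required sample size of at least 532 pupils". The same steps for teachers give a stated design effect of 1.8 and 231 teachers.

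The Data analysis section makes the time × group interaction in a repeated-measures MANOVA the main analysis of primary and secondary outcomes, and names no school or pair term. Clustering enters through one sentence: "In case of a noted cluster effect (intra-cluster correlation coefficient > 0.10) we will use multilevel analysis". Independent t-tests between arms at follow-up come later in the section. The text does not say whether the switch also governs them. Drop-outs are kept in by carrying the last observation forward.

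**The concern.** The two sections treat the same test differently. For sample size, an ICC of 0.05 is taken to inflate the variance of the pupil interaction test about fourfold. For analysis, the same ICC falls below the threshold and pupils are treated as independent. The threshold also has to be read from an ICC estimated on 12 schools, which is too imprecise to choose a method.

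Pupil-reported violence is half of the primary outcome measure. It is also what the Measures against bias section relies on to offset unblinded teacher self-report. If school is ignored, ordinary variation between six schools and six others can appear as an intervention effect with a small p-value and a confidence interval that is too narrow.

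**Working it through.** **Inputs.** From Participants: α = 0.05, power 0.80, f = 0.25, 80 pupils or 20 teachers per school, 20% drop-out, ICC 0.05. From Design of the study: 12 schools in six pairs. From Data analysis: switch at ICC > 0.10; drop-outs retained.

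**Reproducing the plan's figures.**
- A one-df F test at f = 0.25 has power 0.798 at N = 127 and 0.801 at N = 128, so 128 reproduces.
- Pupils: 80 × 0.8 = 64; DE = 1 + 63 × 0.05 = 4.15; 128 × 4.15 = 531.2, rounded up to 532.
- Teachers: 20 × 0.8 = 16; DE = 1 + 15 × 0.05 = 1.75, stated as 1.8; 128 × 1.8 = 230.4, rounded up to 231.

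**Error of a test that ignores school.** A nominal 5% two-sided test whose variance is understated by the factor DE has true type I error 2[1 − Φ(1.96/√DE)].

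| Case | DE | Type I error |
|---|---|---|
| Pupils, 64 per school, ICC 0.05 | 4.15 | 0.336 |
| Pupils, 80 per school (drop-outs retained), ICC 0.05 | 4.95 | 0.378 |
| Pupils, 64 per school, ICC 0.02 | 2.26 | 0.192 |
| Pupils, 64 per school, ICC 0.01 | 1.63 | 0.125 |
| Teachers, 16 per school, ICC 0.05 | 1.75 | 0.138 |

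**Effect of the switch.** Trials with six schools per arm and no effect were simulated. A t-test on individual change was used when the estimated ICC was 0.10 or less, and a t-test on school means otherwise.
- Pupils, ICC 0.05: the switch fires in about 4–5% of trials. The error under the rule is about 0.32 at 64 per school and 0.365 at 80 per school.
- Pupils, ICC 0.10, 64 per school: it fires in about 44% of trials and the error is still about 0.25–0.28.
- Teachers, 16 per school, ICC 0.05: about 0.11–0.12.
- A t-test on school means held about 5% when schools within a pair shared no variance.

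**Sensitivity to what the documents do not give.** Let ρ be the outcome ICC, c the correlation of school effects over time and r the within-school individual correlation over time. The ICC of change is then ρ(1 − c) / [ρ(1 − c) + (1 − ρ)(1 − r)]. With ρ = 0.05, and r = 0.5 by assumption, at 64 pupils per school:

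| c (assumed) | ICC of change | Type I error, school ignored |
|---|---|---|
| 0 | 0.095 | 0.45 |
| 0.5 | 0.050 | 0.34 |
| 0.8 | 0.021 | 0.20 |
| 1 | 0 | 0.05 |

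If half of the between-school variance is shared within regional pairs (assumption, c = 0.5), the error is about 0.21. The independent t-test at follow-up uses no baseline, so stable school differences do not cancel. Without shared pair variance it stays at about 0.34 for every c.

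**Interval width.** At DE 4.15 the unadjusted pupil interval is too narrow by √4.15 = 2.04. Using t rather than normal quantiles, the correction is 2.04 × 2.228/1.96 = 2.3 on 10 df, and 2.04 × 2.571/1.96 = 2.7 on 5 df if pairing explains no variance.

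**The case against.** A reader might infer that the pupil test is certain to have a one-in-three false-positive rate. The documents do not support that. The Participants section does not say which quantity has the ICC of 0.05. A time × group contrast removes stable differences between schools, so the ICC of change may be much smaller. Matching by region may also remove part of the between-school variance. Both arguments stand and are why a range is needed. They do not rescue the rule: the plan itself applies the design effect to the interaction, and within the range shown the error returns to 5% only when school means do not drift differently at all.

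A reader might also infer that the follow-up t-tests are excluded from the switch. The text is silent on this. They are not stated to be covered, and they supplement the interaction test.

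The simulation is a simplification. It uses one change score rather than the MANOVA, does not model carried-forward values, and takes a school-mean test as the multilevel analysis, which the protocol does not specify. The figures therefore illustrate the size of the problem and are not an exact error rate for this plan. The simplifications do not all favour the plan: retaining drop-outs brings the analysed number towards 80 per school and raises the error.

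An unshown analysis plan is no answer, because the conditional rule is stated explicitly here.

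**Conclusion.** The concern holds in conditional form. The protocol's switch turns off the allowance for clustering at the ICC on which the trial was sized. If that ICC applies to the time × group contrast and schools within a pair share no variance, the pupil type I error is about 32–37% under the rule and the teacher error about 11–12%. Under other assumptions the pupil error is 12–19% (change ICC 0.01–0.02) or about 21% (half of the variance shared within pairs). It is close to nominal only without differential drift of school means. P-values and 95% confidence intervals for a primary outcome cannot be relied on under the rule as written, so it should be changed before analysis.

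**What to change.** Delete the ICC > 0.10 condition. State that every between-arm comparison of primary and secondary outcomes, including the follow-up contrast, accounts for school whatever ICC is observed, and reflects the matched pairs. Two forms would do:
- a mixed model with a school random effect, region (pair) as a factor and small-sample degrees of freedom (Kenward-Roger or Satterthwaite); or
- a paired analysis of school-level means on 5 df.

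An unpaired test of school means is not a full substitute. With half of the between-school variance shared within pairs it rejected in only 1.8% of null trials, so it would be conservative. Report the observed ICC descriptively.

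The cost is wording and analysis only, with no new schools, visits or data. At a change ICC of 0.05, pupil confidence intervals become about 2.3 times wider on 10 df, and up to about 2.7 times wider on 5 df if pairing explains no variance.
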